Repetitive transcranial magnetic stimulation (rTMS) as a brain stimulation therapy is recommended for patients with MDD, especially for those who do not respond to pharmacotherapies [12, 13]. The effectiveness of rTMS therapy in the acute phase has already been demonstrated [14–17]. Recently, the possibility of reducing recurrence/relapse by continuing rTMS therapy in the maintenance phase has been investigated [18–28]. A meta-analysis of the long-term effects of acute rTMS in 732 depressed patients in 18 studies found that the proportion of patients who met the treatment response criteria 6 months later was 61.1% (95% confidence interval: 49.8–71.3%) in the group with and 38.5% (21.9–58.3%) in the group without maintenance rTMS [29]. Although the results seem favorable for maintenance rTMS therapy, owing to the small sample size and the heterogeneity of each study, no definite conclusions can be established concerning the efficacy of maintenance rTMS therapy. Considering the sample size, having a large sample size is challenging in a long-term study, such as maintenance therapy, owing to dropouts and other reasons; thus, it is necessary to adopt a feasible design that facilitates participation in the study. Considering heterogeneity, significant differences, especially in the schedule of maintenance therapy, including weekly (or bi-weekly) rTMS versus clustered rTMS, exist. Prior randomized controlled trials have demonstrated a certain level of effectiveness of clustered rTMS as maintenance therapy, with the advantage of reducing the number of hospital visits [30]; however, concerns remain about adverse events, since a greater amount of stimulation is performed in a shorter period of time. Although some case reports and small sample studies exist [18, 28, 31], the efficacy and safety of maintenance treatment with weekly or bi-weekly rTMS therapy remain unknown.

We hypothesized that a weekly or biweekly maintenance rTMS therapy schedule could be effective in preventing depressive relapse/recurrence. Thus, the main objective of this study was to evaluate the efficacy and safety of 12 months of maintenance rTMS therapy in patients with moderate to severe treatment-resistant MDD who respond to acute rTMS therapy with a feasible study design.

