### Participants

#### Inclusion criteria

Participants with MDD above the age of 18 years who responded or remitted to 3–6 weeks of acute rTMS therapy will be included. In Japan, rTMS is indicated for patients who have failed to respond to at least one or more antidepressants; thus, these patients will be included in this study. All the participants must understand and be willing to adhere to the 12-month maintenance therapy schedule. The researchers will obtain informed consent from the participants who meet the criteria.

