#### Exclusion criteria

Possible pregnancy, significant suicidal ideation (suicide item score of Hamilton Rating Scale for Depression 17 item (HAMD-17) ≥ 3), and severe side effects from acute rTMS therapy are the exclusion criteria for this study. Patients with an intracranial implant (e.g., cochlear implants, magnetic clips, stimulators, such as deep brain stimulators) or other metal objects near the stimulation site (e.g., cardiac pacemakers) are contraindicated for rTMS therapy and therefore, patients with these conditions are not eligible for this study.

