### Covariates and outcomes

An overview of the schedule of assessments is shown in Table 1. To ensure the reliability of the assessment, the HAMD-17 and Montgomery–Åsberg Depression Rating Scale (MADRS) will be conducted by clinical or licensed psychologists who have experience in clinical trials. Before the start of the study, we will confirm the agreement of the ratings by using a simulated patient using video clips. In principle, the same evaluator will conduct the evaluation for each participant. In this study, the response is defined as a decrease of 50% or more in the total HAMD-17 score compared to that before the acute phase of rTMS therapy. Remission is defined as a HAMD-17 total score ≤ 7. Relapse/recurrence is defined as a total HAMD-17 score ≥ 14. Cohen's d will be calculated to evaluate the magnitude of the treatment effect for each outcome.

**Table 1 Tab1:** Assessment schedule

	Screening period	Maintenance therapy period				
	1 week	12 months				
	-1 week	0 month	3 month	6 month	9 month	12 month
Screening	◯					
Informed consent	◯					
Patients back ground	◯					
Maintenance rTMS		—△ →	—△ →	—△ →	—△ →	—△ →
Concomitant medications use		★	★	★	★	★
Adverse events		★	★	★	★	★
HAMD-17		◯	◯	◯	◯	◯
MADRS		◯	◯	◯	◯	◯
QIDS		◯	◯	◯	◯	◯
PHQ-9		◯	◯	◯	◯	◯

*HAMD* Hamilton Rating Scale for Depression, *MADRS* Montgomery–Åsberg Depression Rating Scale, *QIDS* Quick Inventory of Depressive Symptomatology, *PHQ-9* Patient Health Questionnaire-9

△: only for maintenance rTMS plus pharmacotherapy group

★: concomitant medication use and adverse events are assessed at each treatment session or outpatient visit

Primary outcome

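### A responder with a pre-acute HAMD-17 of 28 or more can enter already meeting the relapse definition, so the primary event can be recorded without any worsening

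*Protocol article*

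**What the plan says.** All the text is in the protocol article, under Materials and methods.

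- **Entry** (Inclusion criteria): patients "who responded or remitted to 3–6 weeks of acute rTMS therapy will be included". Response alone is enough.
- **Response** (Covariates and outcomes): "a decrease of 50% or more in the total HAMD-17 score compared to that before the acute phase of rTMS therapy". This is relative to each patient's own starting score and has no upper limit.
- **Remission** (same section): "Remission is defined as a HAMD-17 total score ≤ 7".
- **Relapse/recurrence** (same section): "Relapse/recurrence is defined as a total HAMD-17 score ≥ 14". This is absolute. No rise from the enrolment score is required, nor a month-0 score below 14.
- **Exclusions** (Exclusion criteria): the only one based on HAMD-17 is "significant suicidal ideation (suicide item score of Hamilton Rating Scale for Depression 17 item (HAMD-17) ≥ 3", which concerns a single item and not the total score.
- **Population** (Introduction): "patients with moderate to severe treatment-resistant MDD who respond to acute rTMS therapy". No numeric score range is given.

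The primary outcome is the proportion with relapse or recurrence over 12 months. In the outcome list, anyone who has once met the criterion is counted as relapsed at later time points. The primary logistic model adjusts for enrolment status as response or remission and leaves room for further covariates before data fixation. The IPTW sensitivity analysis uses the same covariates.

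**The concern.** A relapse endpoint should record passage from a well state to an ill one. Here the well state is defined by a percentage fall and the ill state by a fixed score, and nothing ties the two together. A severely ill patient who has halved the score can be eligible as a responder and, on the same rating, satisfy the primary event.

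For those participants the primary outcome measures residual symptoms at entry and not loss of benefit. The carry-forward rule then fixes their status at later visits, and time to relapse inherits the problem. Groups are formed by patient preference, so the share of such participants may differ between them. Baseline severity would then show up as part of the treatment comparison.

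**Working it through.** **1. Where the definitions overlap.** The highest score that still counts as response is the integer part of 0.5 × pre-acute score.

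| Pre-acute HAMD-17 | Highest responder score | 14 or more? |
|---|---|---|
| 20 | 10 | no |
| 24 | 12 | no |
| 27 | 13 | no |
| 28 | 14 | yes |
| 30 | 15 | yes |
| 32 | 16 | yes |
| 36 | 18 | yes |

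The overlap starts at 28. A patient who goes from 32 to 16 is eligible. At 16 in month 3, or even improved to 14, the patient is still a responder and also a relapse. Remitters (7 or less) cannot be affected.

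**2. How many participants.** The article states no figure to reproduce and gives no score distribution, so this step rests on assumptions.

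- Assume pre-acute scores with mean 22 or 24 and SD 5, truncated below at 14. The share at 28 or more is P(X ≥ 28)/P(X ≥ 14) = 12.2% (mean 22) or 21.7% (mean 24). This is only the pool in which overlap is possible, because most of these patients, if they respond, will fall well below 14.
- Assume further a mean percentage fall of 40% to 60% with SD 20 to 30 percentage points, and keep those who respond or remit. In simulation, the share of eligible patients entering at 14 or more runs from 1.7% (mean 22, fall 60%, SD 30) to 7.6% (mean 24, fall 40%, SD 20), or about 2% to 8%.

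**3. Equal share in both groups.** Let f be the share entering at 14 or more and counted as events, and p the relapse risk of the rest. The observed rate is f + (1 − f)p, so the difference becomes (1 − f) × 20 points. From Power and sample size calculation: control rate 45% to 60%, effect 20 points, 150 per group, 15% dropout. That leaves 150 × 0.85 = 127.5, taken as 127 per group. Power is for a two-sided test at 0.05.

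| f | Difference (points) | Power, 45% control | Power, 60% control |
|---|---|---|---|
| 0% | 20.0 | 92.1% | 89.5% |
| 2% | 19.6 | 90.6% | 88.2% |
| 5% | 19.0 | 88.1% | 86.3% |
| 10% | 18.0 | 83.3% | 82.6% |

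For f = 5% and a 45% control rate: 0.05 + 0.95 × 0.45 = 47.75% and 0.05 + 0.95 × 0.25 = 28.75%, a difference of 19.0 points.

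**4. Unequal share, no treatment effect.** The false difference is (f₁ − f₂)(1 − p). With 10% versus 5%:

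- p = 45%: 0.05 × 0.55 = 2.75 points
- p = 60%: 0.05 × 0.40 = 2.0 points

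The sign depends on which group holds the larger share.

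**5. Whether the stated adjustment removes it.** The named covariate separates remitters from responders, but not a responder at 8 from one at 16. IPTW on the same list has the same limit. Neither changes the fact that the event is already met at entry.

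**The case against.** The strongest reply is that the affected group is narrow: a pre-acute score of 28 or more together with a fall only just past 50% (at 30, a score of 14 or 15; at 32, 14 to 16). That is right, and it keeps the size small. A reader might take the 12% to 22% who start at 28 or more as the share affected. The documents do not support that, since starting at 28 is not entering at 14.

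A second reply is that imbalance is partly handled: enrolment status is in the model, further covariates may be added, covariate balance after weighting will be checked, and HAMD-17 change is analysed with adjustment for baseline score. This stands as partial mitigation. Month-0 HAMD-17 could be added to the model, but that is not a commitment, and adjustment does not repair an event met before follow-up starts. Against the unmeasured confounding that the Discussion already concedes, the likely bias is modest.

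A third reply is that the full protocol is not shown and might contain a month-0 rule or an entry ceiling. That limits confidence. However, the article prints the entry rule and both definitions, and as printed they overlap.

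A reader might also infer from Table 1, where HAMD-17 first appears at month 0, that patients can drift above 14 between establishing response and time zero. The article does not say which rating settles eligibility, and it could be the month-0 rating. That inference is not supported and forms no part of this point.

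**Conclusion.** The overlap is real on the printed text and begins at a pre-acute score of 28. It makes the primary event invalid for a small subgroup, who can be classed as response and relapse at one visit.

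The size rests on assumed score distributions and probably lies at about 2% to 8% of entrants. The calculation also assumes that these participants remain at 14 or more and are counted as events. On that basis an equal 5% share costs 1 point of the 20-point effect and 3 to 4 points of power. A 10% versus 5% split produces a false difference of 2.0 to 2.8 points. A larger imbalance would require nearly all affected patients to choose the same group, and nothing in the documents suggests that.

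This should be fixed, but it does not overturn the design. A reader might conclude that the trial needs a new entry ceiling. It does not, because the overlap can be resolved in the analysis set. Nor is any view taken here on which relapse threshold is clinically right.

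**What to change.** Before data lock, reconcile Inclusion criteria with Covariates and outcomes by stating who is at risk of the primary event:

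- Restrict the primary relapse/recurrence analysis, the relapse rates at 3, 6 and 9 months and the time-to-relapse analysis to participants whose month-0 HAMD-17 is below the protocol's own relapse threshold.
- Keep the remaining participants in the symptom-score and safety analyses.
- Report a sensitivity analysis of the primary outcome that includes them, and give their number by group.

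The month-0 score is already scheduled and precedes maintenance treatment, so the restriction conditions only on a pre-treatment value and needs no new assessment. The cost is one analysis-set sentence and a few participants lost from the primary analysis. At an assumed 2% to 8%, that is 0.02 × 150 = 3 to 0.08 × 150 = 12 per group of 150.

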### Safety monitoring

An adverse event is defined as any unfavorable medical event that occurs in a participant. A physician will examine the participant at the end of each stimulation and evaluate the adverse events. All the adverse events reported spontaneously by the participant or observed by the research team will be recorded. All the adverse events will be judged based on the intensity and their relation with the investigational product. Serious adverse events are defined as life-threatening events that require hospitalization, result in persistent or significant disability or incapacity, are a congenital anomaly or birth defect, or have a significant impact on the safety of the participant. In the event of serious health problems resulting from participation in this research, the participant may receive compensation benefits from the clinical research insurance coverage provided by the research sponsor.

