## Materials and methods

### Study overview

This study is a multisite, prospective, non-randomized longitudinal trial, recruiting 300 participants, who will be divided into two groups: (I) the maintenance rTMS plus pharmacotherapy group and (II) the pharmacotherapy-only group. The overview of the study is shown in Fig. 1. Only patients who achieve a therapeutic response to acute rTMS therapy will be included in the study. In the maintenance rTMS plus pharmacotherapy group, patients will receive weekly treatments for 6 months, followed by bi-weekly treatments for an additional 6 months, totaling 12 months of maintenance rTMS therapy (maximum 40 sessions). During the maintenance period, the patient will continue with a stable dose of pharmacotherapy. In the pharmacotherapy-only group, patients will receive no intervention other than a continuation of concomitant pharmacotherapy and receive an evaluation. Assessments will be made at 3, 6, 9, and 12 months after the start of maintenance therapy and at the end of study participation. Random allocation to both the groups will not be performed and the patients will be classified to a group (I) or (II) according to their preferences. Owing to the long duration of maintenance therapy immediately following acute treatment in this study, conducting a double-blind, randomized, sham-controlled, parallel-group study was deemed challenging in terms of subject participation and blinding validity.

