#### Secondary and other outcomes

As for the primary outcome, the rates and between-group differences, and adjusted odds ratio (95% CI) will be estimated for the relapse/relapse rate, response rate, and remission rate at 3, 6, and 9 months after enrollment, respectively. Kaplan–Meier curves will be constructed for the duration of the sustained treatment response and sustained remission, and the log-rank test and Cox proportional hazards models will be performed for the between-group comparisons.

The change in the total scores of the HAMD-17, MADRS, QIDS, and PHQ-9 from the baseline (before the introduction of maintenance therapy) will be analyzed using a random-effects model with group, baseline total score, age, sex, time point, and interaction between the time point and the group as explanatory variables and individual as random effect, for all the data at 3, 6, 9, and 12 months.

Frequency distributions of the worst severity of the adverse events and equipment failure will be summarized. Treatment-related adverse events, serious adverse events, and discontinuations owing to adverse events will also be summarized.

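### Adverse-event evaluation is tied to treatment sessions that only the rTMS group has, so side-by-side summaries of events possible in both groups can differ with no true effect

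*Protocol article*

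**What the plan says.** All places are in the protocol article.

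- Safety monitoring: "A physician will examine the participant at the end of each stimulation and evaluate the adverse events". The same section adds: "All the adverse events reported spontaneously by the participant or observed by the research team will be recorded". That sentence is not limited to sessions or to one group.
- Covariates and outcomes, Table 1 footnote: "concomitant medication use and adverse events are assessed at each treatment session or outpatient visit". The table marks adverse events at 0, 3, 6, 9 and 12 months without restriction by group. The maintenance rTMS row is marked "only for maintenance rTMS plus pharmacotherapy group".
- Study overview: the rTMS group has weekly and then biweekly sessions, at most 40 over the year. In the control group, "patients will receive no intervention other than a continuation of concomitant pharmacotherapy and receive an evaluation". For the study as a whole, "Assessments will be made at 3, 6, 9, and 12 months after the start of maintenance therapy and at the end of study participation". No outpatient visit frequency is given for controls.
- The secondary outcomes list adverse events, naming manic and hypomanic episodes by DSM-5 criteria and suicidal ideation alongside stimulation-site complaints and seizure.
- Secondary and other outcomes (analysis): "Frequency distributions of the worst severity of the adverse events and equipment failure will be summarized". No between-group test or estimate for adverse events is stated there.

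**The concern.** Safety stands beside efficacy in the main objective (Introduction), and adverse events are a listed secondary outcome. Some listed events can only arise from stimulation. Others, such as suicidal ideation and manic or hypomanic episodes, can occur in either group, and a reader will compare those across the two columns.

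The collection rule ties active evaluation to a contact that only one group has. The chosen summary is the worst severity over the study. For equal true risk, a maximum taken over more looks tends to be higher. This could make rTMS look less safe than it is for shared events, or hide a real reduction in suicidal ideation. It follows from a rule that the article states, not from a detail left to another document.

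**Working it through.** **1. The plan's own safety figure.** Power and sample size calculation gives a 95% chance of seeing at least one event of 2% probability among 150 rTMS participants. Check: 1 − 0.98^150 = 0.952. The figure reproduces. It concerns the rTMS group alone and is unaffected by this point.

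**2. Contacts per group.** Weekly for 6 months is 26 sessions and biweekly for 6 months is 13, so 26 + 13 = 39, consistent with the stated maximum of 40. The shared assessments after month 0 are four (3, 6, 9 and 12 months). Control outpatient visits come on top of these, in a number not given, so the size can only be shown as a range under assumptions.

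**3. Illustration A: a fixed chance of recording per contact.** Assume each contact records an event with probability q, equal in both groups and independent across contacts. The proportion with at least one recorded event after k contacts is 1 − (1 − q)^k.

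| q (assumed) | 40 contacts (rTMS) | 26 (biweekly) | 12 (monthly) | 4 (3-monthly only) |
|---|---|---|---|---|
| 0.5% | 18.2% | 12.2% | 5.8% | 2.0% |
| 1% | 33.1% | 23.0% | 11.4% | 3.9% |
| 2% | 55.4% | 40.9% | 21.5% | 7.8% |

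This model suits brief, minor complaints. It exaggerates the gap for lasting events, because successive contacts would then see the same event.

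**4. Illustration B: an episode of fixed length.** Assume a 3-week episode, a true 12-month incidence of 10% in both groups, and recording only if a contact falls within the episode. The capture probability is c = min(1, 3 / interval in weeks).

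- Weekly or biweekly contact: c = 1, recorded 10%.
- Every 4 weeks: c = 3/4, recorded 7.5%, apparent ratio 10/7.5 = 1.3.
- Every 13 weeks: c = 3/13, recorded 2.3%, apparent ratio 10/2.3 = 4.3.

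Biweekly control visits would close the gap in this model.

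**5. Effect of recall.** If a missed episode is still reported later with probability r, capture becomes c + (1 − c)r. At r = 0 the figures are those in step 4. At r = 1, capture is 1 and the ratio is 1 whatever the visit interval. The document fixes neither the control interval nor r, so under these assumptions the apparent ratio can lie anywhere from 1 to 4.3.

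**6. Instruments common to both groups.** The HAMD-17, whose suicide item the exclusion criteria already use, is rated in both groups at 0, 3, 6, 9 and 12 months. Table 1 lists no scheduled instrument for mania or hypomania. The exposure to unequal ascertainment is therefore greater for mania than for suicidal ideation.

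**The case against.** The strongest reply is that no between-group adverse-event comparison is planned. The analysis section names group comparisons for relapse, response, remission and time-to-event outcomes, but only summaries for adverse events, and the one quantified safety aim concerns the rTMS group. This stands, and it limits the consequence to how the summaries are read. It does not remove it: the trial has two groups, and summaries set side by side will be compared. The article also says in Covariates and outcomes that an effect size will be calculated for each outcome, without exempting safety.

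A second reply is that spontaneous and observed events are recorded in both groups, and that serious or diagnosed events come to notice without a session. This also stands. It narrows the gap by an unknown amount and weakens the point for severe events, but people seen weekly have more occasions to report mild ones.

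A third is that visit frequency and table layout belong to the full protocol or the SAP. Their absence is indeed no finding. The point rests on the stated rule linking evaluation to sessions.

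Finally, removing session-detected events from the comparison could make harm in the treated group look smaller. That is correct and shapes the fix.

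**Conclusion.** The point holds in a limited form. Adverse-event ascertainment differs by group by design, so summaries of shared events can differ with no true effect. The gap could be sizeable if controls are seen monthly or less often and recall is poor, and small if they are seen about as often as the rTMS group or recall is good. Visit interval, recall, episode length, incidence and recording probability are all assumed; the article gives none of them.

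A reader might infer more, and the documents do not support it:

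- That group rates differ through ascertainment alone. Stimulation-site pain and similar events differ for real reasons.
- That control events are captured only at outpatient visits. The 3-monthly assessments and spontaneous or observed reports also count.
- That the tables are certain to show more and worse events with rTMS, or that a ratio of 1.3 to 4.3 is an estimate. It is an illustration that allows no recall of events since the previous contact.
- That the trial's safety conclusion fails. The aim of detecting rare events in the rTMS group is untouched.

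This is a low-cost improvement to a stated secondary outcome, not a flaw that threatens the trial.

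**What to change.** 1. Keep the full adverse-event summary by group, with every session-detected event included, and label it as reflecting unequal contact.
2. Add a between-group summary restricted to the common 0, 3, 6, 9 and 12 month assessments. Take suicidal ideation from the HAMD-17 suicide item already rated there, for example a score of 3 or more (the cut-off in the exclusion criteria) or worsening from month 0. For mania and hypomania, ask the same question in both groups about episodes since the previous common assessment, so that the recall window is equal.
3. Report stimulation-related events and equipment failure for the rTMS group only, per patient and per session.

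The cost is one standard question at visits that already take place and one extra table. The common-schedule table omits events found only at sessions, so it must be shown beside the full listing and never replace it. It reduces unequal ascertainment but leaves the effects of open-label reporting.

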#### Power and sample size calculation

In the previous meta-analysis of maintenance rTMS therapy, the response rates at 3 and 6 months in the group with and without maintenance rTMS therapy were 76.2% and 61.1%, and 56.1% and 38.5%, respectively [29]. Applying the Weibull distribution to the 3- and 6-month response rates, the 12-month response rate was estimated to be 40.9% for the maintenance rTMS group and 20.7% for the no maintenance rTMS group, with an estimated difference of 20%. Considering the relapse and recurrence rates, the previous randomized controlled trial of maintenance therapy in patients who responded to pharmacotherapy reported 44.4% in the pharmacotherapy-only group and 24.2% in the rTMS maintenance therapy group, with a 20.2% difference between the groups [30]. Based on these previous studies, we estimated that the relapse/recurrence rate without maintenance rTMS was 45–60%, and the add-on effect of maintenance rTMS was 20%. To detect a 20% additional effect of maintenance therapy, the required sample size varies from 109 to 130 patients for a 45 ~ 60% relapse/recurrence rate in the pharmacotherapy-only group (chi-squared test with two-sided alpha = 0.05 and power = 80%). Since this study plans to conduct a multivariable analysis adjusting for the background factors, the power was set as high as 90%. Assuming that the proportion of participants who drop out without any evaluation of efficacy is 15%, the required number of participants would be 150 in each group.

From the viewpoint of detection of rare adverse events in the maintenance rTMS group, with 150 participants, at least one event with a 2% probability with a 95% chance is expected. Therefore, based on the perspective of comparing the efficacy and collecting safety information, the target number of study participants was set at 150 in each group, with a total of 300 participants.

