### Data collection and data management

All the evaluations will be conducted by experienced psychologists. After the data are collected, all the data in the paper files will be transcribed to the Electronic Data Capture system (e Clinical Base; Translational Research Center for Medical Innovation, Kobe, Japan), which is a secure system designed for storage of personal and patient data. The data will be sent to independent data managers to assess whether the data were collected properly, focusing on the status of consent acquisition, eligibility of the participants, evaluation items, and confirmation of drop-out/terminated cases. These data managers will also oversee and review the progress of the trial. If a participant withdraws their consent, they will be dismissed from the study. At the same time, we will record the dropout rate, and the number of participants with adverse events requiring treatment. The Efficacy and Safety Assessment Committee, whose members are independent of the research, will check and assess whether the trial is conducted safely and properly, and will also decide whether to stop the trial if any severe adverse events or protocol violations occur. In addition, an on-site data monitor will conduct monitoring to ensure that the trial is performed properly, data are properly recorded, and data reliability is ensured. Audits will be also conducted independent of the researcher and sponsor. If we conduct any necessary protocol modifications, we will report them to the Clinical Research Review Board, and to the registration site of the Japan Registry of Clinical Trials website. The results of this study will be anonymized and published in relevant academic conferences and journals.

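### As worded, every serious adverse event criterion is conditional on a threat to life and death is not named, so literal use would under-count serious events

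*Protocol article*

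**What the plan says.** Under Safety monitoring the article gives its only definition of seriousness: "Serious adverse events are defined as life-threatening events that require hospitalization, result in persistent or significant disability or incapacity". The sentence continues that such events "are a congenital anomaly or birth defect, or have a significant impact on the safety of the participant". The same section has every adverse event captured, "All the adverse events reported spontaneously by the participant or observed by the research team will be recorded", and has each one judged for intensity and for its relation to the investigational product.

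The definition feeds an analysis output. Secondary and other outcomes says: "Treatment-related adverse events, serious adverse events, and discontinuations owing to adverse events will also be summarized". The same paragraph summarises the worst severity of adverse events as a separate item.

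Under Data collection and data management, an independent committee checks that the trial is run safely and properly, and "will also decide whether to stop the trial if any severe adverse events or protocol violations occur".

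**The concern.** A definition of seriousness normally works as a list of alternatives: an event that meets any one of them is serious. Here the threat to life has become the noun phrase that the whole list describes. An event then has to be life-threatening and also meet one of the items.

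The document's own outcomes show what could be affected. The safety outcomes include suicidal ideation, seizure, and manic or hypomanic episodes. Each can lead to an admission without an immediate threat to life, and such an admission fails the printed test. Safety is part of the stated main objective, and serious events are a reported category of their own, so the definition sets that count. If some sites applied the sentence literally and others applied its evident intent, the counts would also not be comparable between sites.

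A second, smaller point concerns vocabulary. The article keeps intensity apart from seriousness, but the committee passage uses the intensity word, and it is unclear which of the two is meant.

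**Working it through.** The point rests on wording, and the plan states no figure for serious events that could be reproduced.

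**Step 1: structure of the definition.** The sentence has the form: life-threatening events that [A, B, C, or D], where A is hospitalisation, B is disability or incapacity, C is congenital anomaly or birth defect, and D is a significant effect on participant safety. The restrictive clause covers all four items. Literally, therefore, serious = life-threatening AND (A or B or C or D). The usual structure would be serious = death OR life-threatening OR A OR B OR C OR D.

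**Step 2: what each reading counts.**

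| Event | Literal reading | Criteria as alternatives, death named |
|---|---|---|
| Hospitalisation, no threat to life | not serious | serious |
| Lasting disability, no threat to life | not serious | serious |
| Congenital anomaly, no threat to life | not serious | serious |
| Life-threatening event | serious (at least through D) | serious |
| Death | only if read as life-threatening | serious |

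Criterion D does not rescue the first three rows, because it sits under the same qualifier. On the literal reading A, B and C do almost no work, since any life-threatening event already satisfies D. That suggests the literal reading was not intended.

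**Step 3: is it corrected elsewhere?** No other section of the article defines a serious adverse event or lists death.

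**Step 4: where the count is used.** Secondary and other outcomes reports serious events separately, so an event in the first three rows would be absent from that summary. It would remain in the adverse event records and in the worst-severity distribution.

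**Step 5: size.** If h is the number of hospitalisations and f the fraction of them that are life-threatening, the literal count omits h × (1 − f). The document gives neither h nor f, so the size cannot be computed.

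An illustration can borrow the article's own rare-event figure (Power and sample size calculation): "with 150 participants, at least one event with a 2% probability with a 95% chance is expected". That figure reproduces: 1 − 0.98^150 = 0.952. Assume, for illustration only, that hospitalisation is such an event, so that 150 × 0.02 = 3.0 are expected, and that f is 10%, 25% or 50%:

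- f = 10%: 3.0 × 0.10 = 0.3 counted; chance of counting at least one is 1 − 0.998^150 = 26%
- f = 25%: 3.0 × 0.25 = 0.75 counted; 1 − 0.995^150 = 53%
- f = 50%: 3.0 × 0.50 = 1.5 counted; 1 − 0.99^150 = 78%

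These figures show only how the mechanism works. They do not estimate what will happen in this trial.

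**Step 6: severe and serious.** Safety monitoring grades intensity for all adverse events and defines seriousness separately. Secondary and other outcomes likewise reports worst severity and serious events as two items. The committee passage names severe events only. The text does not show whether this means high intensity or the defined serious category.

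**The case against.** The strongest reply is that this is a slip of the pen, probably a missing comma or conjunction after the first criterion. The list makes sense only as alternatives, and staff may well read it that way. The article also condenses a fuller protocol that is not shown and may define seriousness correctly. Both points are fair and limit the consequence: an actual under-count is not demonstrated. They do not remove the error. The article printed a definition, and the definition is wrong as printed. If the full protocol is right, the article disagrees with it and still needs correcting.

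The second reply is that the events are caught elsewhere. All adverse events are recorded and graded, suicidal ideation and seizure are named outcomes whatever their seriousness, and participants with adverse events needing treatment are counted. This stands. A reader might infer that safety events would be lost; the document does not support that. They would be misclassified, and the effect is confined to the serious event summary. The primary outcome and the efficacy comparisons are untouched.

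Third, the absence of death is the weaker half. A fatal event can be read as life-threatening, so it does not follow that deaths would go uncounted. The defect is that their inclusion is left to inference.

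Fourth, a reader might infer that the committee's decision to stop the trial depends on this definition. The text does not show that. The committee passage refers to severe events, and that word may be deliberate, since intensity is graded. What remains is an ambiguity to resolve.

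**Conclusion.** The point holds as a misstated definition. As printed, a threat to life is required for every serious adverse event and death is not named. On a literal reading, hospitalisations and lasting disabilities without a threat to life would be missing from the serious adverse event summary, while remaining in the general adverse event records.

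The conclusion assumes that the sentence is applied as written; whether sites do so cannot be known from the article. The size of any under-count is not computable, and no number of omitted events should be attached to it. The wording is probably a slip. Correction is still worthwhile because the definition governs a reported safety count and the trial is listed as ongoing. The wording on severe and serious events is a separate matter of unclear meaning.

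**What to change.** Rewrite the sentence under Safety monitoring so that an event is serious if it meets any one of these:

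- it results in death;
- it is life-threatening;
- it requires hospitalisation;
- it results in persistent or significant disability or incapacity;
- it is a congenital anomaly or birth defect;
- it has a significant impact on participant safety.

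Check the revised sentence against the full protocol so that the two agree. Separately, reconcile the committee passage under Data collection and data management with Safety monitoring and with Secondary and other outcomes, and state whether intensity or seriousness is meant there. This review takes no position on which it should be.

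The cost is a change of wording and possibly more events reported as serious. The sample size and the efficacy analyses do not change.
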